**Methods/design:**

In total, 800 patients with a stable course of rheumatoid arthritis or psoriatic arthritis in 20 centers in North Rhine–Westphalia and Lower Saxony will be randomized to either nurse-led care or standard care. Participating nurses will study for a special qualification in rheumatology and trial-specific issues. It is hypothesized that nurse-led care is non-inferior to standard care provided by rheumatologists with regard to a reduction of disease activity (DAS28) while it is hypothesized to be superior regarding changes in health-related quality of life (EQ-5D-5L) after 1 year. Secondary outcomes include functional capacity, patient satisfaction with treatment, and resource consumption.

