### Secondary outcomes

Secondary outcomes include other established assessments in rheumatology, as well as evaluations of organizational issues, patient satisfaction with medical treatment, and resource consumption.

One of the most important prognostic markers in rheumatoid arthritis is physical functioning, which will be measured by the validated Hannover Physical Functioning Questionnaire (FFbH) [9]. This assessment is comparable to the internationally applied Health Assessment Questionnaire (HAQ) [10]. Patients are asked, if they are able to perform 18 activities of daily living. They answer on a three-point scale (“yes,” “yes, but with difficulty,” and “no or only with assistance”). The patient’s physical activity will be assessed via the PRISCUS Physical Activity Questionnaire (PAQ) [11], which has ten items that assess the time spent in domestic activities (e.g., housework), sporting activities (e.g., riding a bicycle), and inactivity (e.g., sedentary activity) during the prior week. The tendency to depressive moods is assessed by the two-item Patient Health Questionnaire (PHQ-2) [12]. Further patient-related outcomes are the patient’s estimate of (1) disease activity (numeric rating scale 0–10 [NRS]), (2) pain (NRS), (3) fatigue (NRS), (4) sleep disturbances (NRS), and (5) duration of morning stiffness. The C-reactive protein (CRP) is a standard feature of laboratory analyses, and it will be assessed in the course of the intervention. Smoking status may influence the course of chronic inflammatory diseases and will be subject of patient education by the nurse. Therefore, it will be assessed as a secondary outcome.

In addition, patients will be asked about how long they need to wait for an appointment in their practice, the availability of the rheumatologist or the nurse for inquiries, their satisfaction with the information provided, their satisfaction with their relationship with the rheumatologist or the nurse, and their satisfaction with the coordination and communication done by the different professional groups.

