These outcomes are compared to direct and indirect costs and other resource consumption (e.g. duration and costs of nurse-led care vs. standard care). A EULAR recommendation [4] is “to perform cost-effectiveness studies across different European countries, on the role of the nurse in basic and advanced practice.” There are already British [5] and Dutch [13] but no German studies on the costs and efficiency of nurse-led care in rheumatology. Within this study, an economic evaluation will be done using the Questionnaire for Health-Related Resource Use in an Elderly Population (FIMA) [14]. The components of FIMA are as follows: (1) outpatient medical care, (2) remedies, (3) nursing and domestic care, (4) semi-residential care (daycare) and short-term care, (5) benefits of statutory nursing-care insurance, (6) medication, (7) rehabilitation measures, (8) (partly) inpatient hospitalization, (9) medical aids, (10) relocation, (11) type of housing, and (12) periods of incapacity for work.

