### Statistical analysis

This trial has a two-part primary endpoint that will be hierarchically tested. Non-inferiority of the intervention group compared to the standard care group will first be examined regarding the difference in disease activity (DAS28) after 1 year. A *t*-test of non-inferiority (one-sided, α = 0.025, non-inferiority-margin 0.4 in the DAS28 score) will be performed. The analysis population consists of those who completed the study per protocol.

If nurse-led care is found to be non-inferior, its superiority over standard care will be tested with regard to health-related quality of life (EQ-5D-5L). This analysis will be performed with all randomized patients based on the intention-to-treat principle using multiple imputation.

The analysis of the secondary outcomes will use all available data for the per protocol population. Continuous data will be compared for the two groups using an analysis of covariance adjusting for baseline data. Analyses of categorical variables or proportions will be performed using a chi-squared test. An additional repeated-measures analysis will be done for all quantitative endpoints taken at different time points. Details of the primary, secondary, and all additional analyses are documented in the statistical analysis plan.

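### Secondary outcomes, including satisfaction and resource use, are confined to the per-protocol population although they are margin-free comparisons in an open trial, which leaves them open to selection bias

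*Protocol article*

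**What the plan says.** The Statistical analysis section of the protocol article fixes three analysis populations:

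- **DAS28 (first primary outcome, non-inferiority):** "The analysis population consists of those who completed the study per protocol".
- **EQ-5D-5L (second primary outcome, superiority):** "This analysis will be performed with all randomized patients based on the intention-to-treat principle using multiple imputation".
- **Secondary outcomes:** "The analysis of the secondary outcomes will use all available data for the per protocol population". Continuous ones are compared by baseline-adjusted analysis of covariance, categorical ones by chi-squared test. No margin is given for any of them.

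Resource consumption falls under the third rule. The abstract says "Secondary outcomes include functional capacity, patient satisfaction with treatment, and resource consumption", and the Secondary outcomes section again lists "evaluations of organizational issues, patient satisfaction with medical treatment, and resource consumption". The economic part of that section follows the secondary outcomes and says "These outcomes are compared to direct and indirect costs and other resource consumption". It names neither an effect measure nor a population for the economic evaluation.

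The Data collection section places EQ-5D-5L, satisfaction, organisational procedures and resource consumption in one telephone interview at baseline, 26 and 52 weeks. The Assignment of interventions section states that patients and care providers are not blinded.

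**The concern.** A per-protocol set has a recognised place in a non-inferiority test, because deviations and dropout tend to make the arms look alike. That reason does not carry over to a test for a difference without a margin. There, dropping patients after randomisation gives up the protection of randomisation, and the per-protocol set is not the conservative choice. The protocol follows this logic for EQ-5D-5L but not for the secondary outcomes, and gives no reason. Answers from a single telephone call would be analysed in two populations.

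Exclusion could plausibly depend on the arm. Allocation is known to patients and staff. The Interventions section monitors adherence through attendance at routine checks. Nurse appointments are set at every 3 months, while the standard-care section describes that interval as the usual one.

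The affected results carry weight. The Evaluation of delegation section reads the success of delegation from the secondary as well as the primary outcomes and names patient satisfaction. The abstract and Discussion look ahead to cost-effectiveness and adoption as standard practice.

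**Working it through.** **1. The plan's own figure.** Inputs from the Sample size section: SD 1.7, margin 0.4, one-sided alpha 0.025, power 90%, dropout 5%. With a true difference of zero:

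n per arm = 2 × 1.7² × (1.960 + 1.282)² / 0.4² ≈ 379.6, so 380.

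After dropout: 380 / 0.95 = 400 per arm, 800 in total. All three stated figures reproduce (the exact t calculation gives 381). The concern disputes none of them. An analysis of all randomised patients would use 400 per arm. The per-protocol set would hold about 380 if exclusions equalled the planned 5% dropout, and fewer if deviations are also excluded.

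**2. Bias from exclusion.** Let d be the share excluded from an arm and g the difference in mean outcome, retained minus excluded, in SD units. Then:

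full-arm mean = (1 − d) × retained mean + d × (retained mean − g) = retained mean − d × g.

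The per-protocol mean is therefore shifted by d × g, and the bias in the contrast is b = d(nurse) × g(nurse) − d(standard) × g(standard).

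**3. Type I error.** With 400 randomised per arm and no true difference among all randomised patients:

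SE = √(1/n(nurse) + 1/n(standard)), and error = Φ(−1.96 − b/SE) + 1 − Φ(1.96 − b/SE).

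This is a normal approximation, two-sided at 5%, without baseline adjustment. Every d and g below is an assumption. The document gives only the 5% dropout rate.

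| Excluded, nurse / standard | Gap g | Retained n | Bias (SD) | Type I error |
|---|---|---|---|---|
| 5% / 5% | 0.5 in both arms | 380 / 380 | 0 | 5.0% |
| 5% / 5% | 0.5 in nurse arm only | 380 / 380 | 0.025 | 6.4% |
| 10% / 5% | 0.5 in both arms | 360 / 380 | 0.025 | 6.3% |
| 15% / 5% | 0.5 in both arms | 340 / 380 | 0.05 | 10.3% |
| 15% / 5% | 1.0 in both arms | 340 / 380 | 0.10 | 26.8% |

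Fourth row in full: b = (0.15 − 0.05) × 0.5 = 0.05. SE = √(1/340 + 1/380) = 0.0747, so b/SE = 0.67. Error = Φ(−2.63) + 1 − Φ(1.29) = 0.004 + 0.099 ≈ 0.103.

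**4. The same mechanism for costs.** Assume retained patients cost 1.0 unit and excluded patients 3.0.

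- With 10% excluded under nurse-led care and 5% under standard care, the true means are 0.90 × 1 + 0.10 × 3 = 1.20 and 0.95 × 1 + 0.05 × 3 = 1.10. The per-protocol means are 1.00 in both arms, so a real difference of 0.10 disappears.
- With 5% excluded in each arm, the true means are 1.10 and 1.10, and the difference is zero in either set.

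**The case against.** **The analysis plan may cover this.** The article defers details to a statistical analysis plan that is not shown, and an analysis of all randomised patients may be among its additional analyses. That cannot be ruled out. But the article does not leave the population open: it states the per-protocol set and mentions no other for the secondary outcomes.

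**No superiority is claimed for these outcomes.** The Main hypotheses section covers only the two primary outcomes, and the Evaluation of delegation section asks whether nurse-led care is as effective as standard care. This stands as to the label. The tests are still margin-free comparisons, so the non-inferiority argument for a per-protocol set does not apply.

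**The size is assumed.** This stands. With exclusions near 5%, balanced in number and prognosis, there is no between-arm bias.

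**Imputation is no cure-all.** This stands for patients who left: values are recovered only as far as the observed data predict them. Patients who deviated but still gave the interviews would return with real data.

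Three stronger readings are tempting, and the document does not support them:

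- *Costs and effects come from different patients.* The economic text follows the secondary outcomes and does not name EQ-5D-5L as the effect measure. If the effects are those secondary outcomes, both sides share the per-protocol set. If EQ-5D-5L is used, the analysis sets would differ as stated, but one is nested in the other.
- *Hospitalised patients, or those referred back to the rheumatologist, are excluded.* No section defines these events as deviations. The nurse-led care section makes hospital management and contact with the rheumatologist part of the intervention.
- *Satisfaction is biased upward and costs downward.* The direction depends on who is excluded in each arm, which is not given.

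**Conclusion.** The concern holds in a limited form. The protocol article sets a per-protocol population for margin-free secondary comparisons in an open trial, and this is at odds with its own choice for EQ-5D-5L. These comparisons are open to selection bias. They are not shown to be biased.

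The size is conditional. It is nil when exclusions are balanced in number and prognosis. It is small (type I error about 6%) at 10% against 5% excluded with a 0.5 SD gap. It is material (about 10%, or 27% with a 1.0 SD gap) at 15% against 5%. These figures rest on assumed exclusion rates and gaps, and on an unadjusted normal approximation.

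A mismatch between costs and effects would be added only if EQ-5D-5L is the effect measure of the economic evaluation. The sample size and the DAS28 analysis are not affected by this point.

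**What to change.** In the Statistical analysis section, replace the sentence on the secondary-outcome population with three statements:

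1. Secondary outcomes and resource use are analysed in all randomised patients as allocated, with missing data handled by multiple imputation as already planned for EQ-5D-5L.
2. The per-protocol analysis is shown as a sensitivity analysis.
3. The economic evaluation names its effect measure and uses one common population for costs and effects.

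The number and baseline profile of patients outside the per-protocol set should be reported by arm, since the size of any bias depends on them.

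The cost is a change of a few sentences, some extra imputation work, and reliance on the missing-at-random assumption for patients who left. No new data and no change in sample size are needed. The change should be made and dated before the analysis starts, while the analysts are still blinded.

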### Assignment of interventions

Patients who are correctly enrolled via screening fax and have completed a telephone interview will be randomized by the data management center to either standard care or nurse-led care. Randomization will be performed using blocks with a variable block length stratified by center. The allocation sequence is accessible only to members of the data management team. Study centers will be informed by fax of the group allocation of each patient before their baseline visit.

In this study, trial participants and care providers cannot be blinded to group allocation. The outcome assessors will be blinded. Patients are asked not to tell the assessor or the call center agents to which group they are assigned. Data analysts are also blinded.

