**Fig. 1 Fig1:**
[figure not shown]
Schedule of enrolment, interventions, and assessments. A blinded assessor, BSA body surface area, CDAI Clinical Disease Activity Index, CRP C-reactive protein, DAS28 28-joint Disease Activity Score, EQ-5D-5L Five-dimension Five-level Quality of Life, ESR erythrocyte sedimentation rate, FFbH Hannover Physical Functioning Questionnaire, FIMA Questionnaire for Health-Related Resource Use in an Elderly Population, NRS numeric rating scale, O physician or nurse according to allocation, P patient, PAQ Physical Activity Questionnaire, PHQ-2 Two-item Patient Health Questionnaire, TI telephone interview

At the beginning and at the end of the intervention for a participant, the first primary outcome, DAS28, will be assessed by a blinded external assessor in the practice or outpatient clinic. The assessors are qualified assistant doctors from the Herne Rheumatology Center. They are trained in performing standardized assessments using DAS28 and have received a written copy of the standard operating procedures.

The other primary outcome, health-related quality of life, and secondary outcomes, including organizational procedures, patient satisfaction, and resource consumption, will be assessed via a computer-assisted standardized telephone interview at baseline as well as after 26 and 52 weeks.

The patient will be asked to complete questionnaires at baseline, after 6 months, and at the end of the intervention. Each questionnaire asks about secondary outcomes, such as smoking status, physical functioning, physical activity, depression, estimation of disease activity, intensity of pain, fatigue, tiredness, sleep disturbances, and duration of morning stiffness. The patient additionally provides sociodemographic information at baseline.

The rheumatologist or the nurse will document the participant’s age, gender, height, and weight at baseline. Furthermore, they will assess the CRP as a secondary outcome, (new) comorbidities, the CDAI (and body surface area as necessary), or death of the patient at each routine control examination every 3 months.

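### Categorical secondary outcomes get an unadjusted chi-squared test although baseline status is recorded: valid, but inefficient for stable outcomes such as smoking status

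*Protocol article*

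**What the plan says.** The Statistical analysis section of the protocol article sets three rules for secondary outcomes.

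- Continuous outcomes: "Continuous data will be compared for the two groups using an analysis of covariance adjusting for baseline data".
- Categorical outcomes: "Analyses of categorical variables or proportions will be performed using a chi-squared test".
- Repeated measurements: "An additional repeated-measures analysis will be done for all quantitative endpoints taken at different time points". This covers quantitative endpoints only.

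The section then refers to a further document: "Details of the primary, secondary, and all additional analyses are documented in the statistical analysis plan".

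Smoking status is declared a secondary outcome under Secondary outcomes, with the reason that "Smoking status may influence the course of chronic inflammatory diseases and will be subject of patient education by the nurse". Under Data collection, "The patient will be asked to complete questionnaires at baseline, after 6 months, and at the end of the intervention", and "Each questionnaire asks about secondary outcomes, such as smoking status". A baseline value is therefore held for each patient who returns the first questionnaire.

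Under Assignment of interventions, "Randomization will be performed using blocks with a variable block length stratified by center".

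**The concern.** Baseline adjustment reaches continuous secondary outcomes and stops short of categorical ones, and no reason is given. For an outcome that most patients carry unchanged from entry to one year, a crude comparison of final status mainly compares who smoked at entry. Randomisation balances that on average, but its chance variation stays in the standard error and can swamp the change that nurse education is meant to produce. The test also leaves out centre, the factor on which randomisation was stratified.

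What is at stake is efficiency in a secondary comparison. A real effect on smoking could go undetected although the data that would sharpen the test are already collected.

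**Working it through.** **The plan's own figure.** The Sample size section gives SD 1.7, margin 0.4, one-sided α = 0.025 and 90% power. Per arm, n = 2 × (1.960 + 1.282)² × 1.7² / 0.4² ≈ 380, and 380 / 0.95 = 400. Both stated figures reproduce. They concern DAS28; the article gives no power for any categorical outcome. I use 380 per arm below.

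**Assumptions, none from the documents.** Smoking prevalence at entry b = 20%, the same share s of non-smokers starting in both arms, and quit rates q_C (standard care) and q_N (nurse-led care). The test is two-sided at 5% on smoking status at one year.

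**Formulas.**
- Prevalence at one year in an arm: p = b(1 − q) + (1 − b)s.
- Difference between arms: d = b(q_N − q_C).
- Crude variance per patient: V_crude = p̄(1 − p̄), with p̄ the mean of the two prevalences.
- Variance within baseline strata: V_strat = b·q̄(1 − q̄) + (1 − b)·s(1 − s), with q̄ the mean quit rate.
- Standard error: √(2V/380). Power ≈ Φ(d/SE − 1.96) + Φ(−d/SE − 1.96).

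**Worked case: quitting 10% vs 30%, 1% starting.**
- p_C = 0.20 × 0.90 + 0.80 × 0.01 = 0.188; p_N = 0.20 × 0.70 + 0.80 × 0.01 = 0.148; d = 0.040; p̄ = 0.168.
- V_crude = 0.168 × 0.832 = 0.1398; SE = 0.0271; d/SE = 1.475; power 31%.
- V_strat = 0.20 × 0.20 × 0.80 + 0.80 × 0.01 × 0.99 = 0.0399; SE = 0.0145; d/SE = 2.76; power 79% (simulation: 80%).

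The effect d is the same in both lines. Only the variance changes, and stratifying removes about 71% of it (0.0399 / 0.1398 = 0.286).

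**All cases.** The last two columns are simulated; the formula agrees with them to within about one point.

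| Quit rates | Starting | p_C, p_N | V_crude | V_strat | Crude power | Baseline-stratified power |
|---|---|---|---|---|---|---|
| 10% vs 20% | 1% | 0.188, 0.168 | 0.1463 | 0.0334 | 11% | 32% |
| 10% vs 25% | 1% | 0.188, 0.158 | 0.1431 | 0.0368 | 19% | 58% |
| 10% vs 30% | 1% | 0.188, 0.148 | 0.1398 | 0.0399 | 31% | 80% |
| 20% vs 40% | 5% | 0.200, 0.160 | 0.1476 | 0.0800 | 30% | 49% |

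In the control arm, the correlation (phi) between baseline and 1-year status is 0.91 in the first three rows and 0.75 in the last. The relative loss of power is 1 − 11/32 = 66%, 67%, 61% and 39%.

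**Weaker tracking.** With correlation r, adjustment multiplies d/SE by about 1/√(1 − r²). A comparison with 50% crude power rises to 54% at r = 0.3, 62% at r = 0.5 and 78% at r = 0.7.

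**Validity.** With no treatment effect, both the crude and the stratified test reject in about 5% of simulated trials.

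**Centre.** Simulation with 20 equal centres, 19 patients per arm in each, average prevalence 50% and log odds ratio 0.4, all assumed except the number of centres:

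| Between-centre SD (logit) | Real size of the crude test | Crude power | Centre-stratified power |
|---|---|---|---|
| 0.5 | 4.2% | 74% | 75% |
| 1.0 | 3.0% | 64% | 71% |
| 1.5 | 2.2% | 49% | 63% |

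In the smoking scenarios, stratifying by centre alone moved power by about one point. Stratifying by baseline × centre cells cost about 2 to 7 points against baseline alone, because the cells are sparse.

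**The case against.** The strongest case on the other side has four parts.

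1. The article names a test but does not define the smoking endpoint. A chi-squared test of quitting among baseline smokers would also fit the sentence, and under the same assumptions its power is 41%, 69% and 88% for the three 1%-starting cases. This narrows the point to comparisons of 1-year status. It does not remove it: the article does not state that endpoint, and the endpoint is efficient precisely because it uses the baseline value.

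2. Details are left to a statistical analysis plan that is not shown and may add adjusted models. That is fair. Still, the article itself fixes the unadjusted test, and a plan consistent with that sentence would use it.

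3. A reader might infer that most of the power is lost for categorical outcomes in general, or that a real smoking effect would be caught with adjustment. The documents support neither. They give no smoking rates; the relative loss falls to 39% at phi 0.75, and the gain is small when tracking is weak. Adjusted power is still only 32% for 10% vs 20%. Smoking is also the only clearly categorical secondary outcome: waiting time is a duration, and no response scale is given for satisfaction or availability.

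4. A reader might infer that ignoring centre makes the p-values materially too conservative. That needs a logit SD of about 1 or more between centres, which the documents do not suggest. At 0.5 the effect is negligible.

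All four limit the size of the point. The unexplained difference in treatment between continuous and categorical outcomes remains.

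**Conclusion.** The point holds as a minor efficiency matter. The plan adjusts continuous secondary outcomes for baseline and leaves categorical ones unadjusted, although smoking status is measured at entry and is a stated target of the intervention. If smoking is compared as 1-year status and is stable over the year, the crude test has well under half the power of a baseline-stratified one in the assumed cases with 1% starting. With less stability it keeps about three fifths (30% against 49%). These figures rest on assumed prevalence, quitting and starting rates and on 380 patients per arm.

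The crude test is valid, no primary conclusion is affected, and the trial was not sized for these outcomes. Centre is a secondary matter of matching the analysis to the design.

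**What to change.** Replace the sentence on categorical variables along these lines:

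- Where a baseline value was measured, use logistic or ordinal logistic regression with treatment and baseline value, or a Cochran-Mantel-Haenszel test stratified by baseline status. Enter centre as a random effect, or pool small centres.
- Where there is no baseline value, use a Cochran-Mantel-Haenszel test stratified by centre.
- Report the adjusted odds ratio or risk difference with its 95% confidence interval, and keep the crude chi-squared test as a check.

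The cost is a sentence or two in the analysis section or the statistical analysis plan, with no new data. The downsides are slightly more modelling and the need to handle sparse centres. In particular, full baseline × centre stratification should be avoided, since it gives back part of the gain.
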